**5.6 Outcome measures**

A. Number of BSI/CLABSI/clinical sepsis events per 1000 patient days during the intervention periods compared with the control periods.

B. Number of new patients colonized with MRSA, VRE, CRAB or ESBL per total number of patients, monthly range and variance.

C. Number of new patients colonized with MRSA, VRE, CRAB or ESBL per 1000 eligible patient days [ Total patient days – total patient days for patients identified with MDRO]

D. Time to colonization with MDRO during the intervention periods compared with the control periods.

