**4. Expected significance**

National data from the USA indicate that almost a quarter of very low birth weight infants will have one or more episodes of sepsis. Compared with infants without sepsis, infants with sepsis had a significantly longer hospital stay (79 vs.60 days), had a 2-fold increase in the number of days on mechanical ventilation, and had a significantly higher mortality rate (18% vs 7%)3. Another American study estimated that, on average, the cost of NICU care was $16,800 greater per infant who experienced NICU-associated BSI^[[32]](#endnote-32)^. Approximately 7% of infants, or >12,000 infants, are born prematurely in Israel every year^[[33]](#endnote-33)^. Extrapolating the American data to the Israeli NICU translates into a major health problem. The Ministry of Health and the Israel Neonatal Society have recently launched a national program aimed at minimizing the rate of NI in the Israeli NICUs^33^. In our NICU we have adopted this program and have increased staff education, active monitoring of compliance with guidelines, as well as adoption of the “search and isolate” policy, with twice a week screening of patients for colonization with MDRO.

Despite these measures, BSI rates remain high in our NICU, which prompt us to search for additional interventions such as CHG baths. The goal of the currently proposed study is to determine if universal use of a chlorhexidine based bathing system for patients in the NICU will decrease skin bacterial burden and lead to decreased horizontal transmission of MDRO.

Additionally, we hypothesize that reduced skin colonization with opportunistic bacterial

pathogens will result in a reduction in the rate of CLABSI, BSI and clinical sepsis in comparison to regular bathing procedures.

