**5.7 Data collection**

Each patient admitted to the NICU during the study periods and meeting the inclusion criteria, will be recorded and assigned a specific study number. The dates of admission and dates of discharge will be recorded and used to calculate length of stay and to determine the

incidence of nosocomial infections based on microbiological data. Clinical and laboratory data, including the use of invasive device (intravascular devices, mechanical ventilation, feeding tubes) will be collected on standardized forms. The data will be coded under a password protected database and linked only to study patient identifier.

Infections and MDRO acquisitions will be monitored during the study period. Events occurring within 2 days after the transition will be assigned to the previous bathing period.

For infection surveillance, daily review of cultures and new orders for antibiotic therapy will be performed for all study participants. Infectious events will be evaluated by an independent investigator blinded to the intervention period.

Active surveillance testing for MDRO will be performed once every two weeks during the study period. Swabs from the nasopharynx (for MRSA)] and from the rectal area (for ESBL producing organisms, VRE and CRAB) will be obtained by unit staff and processed in the microbiology laboratory of Shaare-Zedek Medical Center.

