**5.9 Statistical analyses**

Changes in the rates of BSI and clinical sepsis will be compared between the intervention and the control period. Continuous variables will be examined with the use of two-sample t-tests and linear regression modeling, and categorical variables will be examined by means of Fisher’s exact test. Cox proportional-hazards regression model will be used to compare the time from admission until the first primary bloodstream infection , clinical sepsis or acquisition of MDRO between the control and intervention periods.

**Sample size calculation:** based on our ongoing surveillance, there are 2-3 BSI events per 1000 patients –days in our NICU. In order to detect a 50% reduction in BSI rates , we will need 37,096 patient days (18,548 in each group) in order to have 80% power to reject the null hypothesis, with 0.05 level of significance. Currently, our average annual census is 45,000 patient days. therefore, a 2-year study will have >80% power to reject the null hypothesis (the BSI rates in the control period equal the rates in the intervention period).

**For the preliminary study, we used the data in Milstone et al. ^18^ who reported no serious adverse skin reactions and an incidence of 1.2 minor skin reactions per 1000 patient days. A sample of 500 patient days will enable us to detect a ten-fold higher rate of minor skin reactions. Therefore at least 200 patient days in each group of the preliminary study (>600 patient days), would suffice.**

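### MDRO outcomes B and C count infants never swabbed and days after the last two-weekly swab as colonisation-free, which makes B too low and leaves C wrong in a direction that depends on the true rate and the length of stay

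*Protocol*

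**What the plan says.** Section 5.7 sets the detection schedule: "Active surveillance testing for MDRO will be performed once every two weeks during the study period". It names no swab at discharge. The only time data it specifies are dates of stay: "The dates of admission and dates of discharge will be recorded and used to calculate length of stay".

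Section 5.6 then writes the denominators. Outcome B is "Number of new patients colonized with MRSA, VRE, CRAB or ESBL per total number of patients". Outcome C is the number of newly colonised patients "per 1000 eligible patient days [ Total patient days – total patient days for patients identified with MDRO". Neither is limited to infants who were swabbed or to time up to an infant's last swab.

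Outcome D is "Time to colonization with MDRO during the intervention periods compared with the control periods". Section 5.9 uses a Cox model to "compare the time from admission until the first primary bloodstream infection , clinical sepsis or acquisition of MDRO". Neither section states a censoring date.

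Two other statements bear on detection. Section 4 describes the unit's adopted policy as "twice a week screening of patients for colonization with MDRO", which does not match section 5.7. Section 5.7 also provides that "daily review of cultures and new orders for antibiotic therapy will be performed for all study participants", introduced as part of infection surveillance.

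**The concern.** A colonisation rate is sound only if the denominator holds the infants and the time in which a colonisation could have been found. Here the numerator is filled at swab rounds up to 14 days apart, while the denominators run over every patient and, for infants never identified, every day to discharge. An infant who comes and goes between two rounds is never tested, yet enters B as uncolonised and gives all its days to C. An infant who is swabbed, then acquires an organism and leaves before the next round, is handled in the same way.

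The shortfall depends on length of stay and swab spacing, not on bathing. The MDRO rates therefore cannot be read as acquisition rates or compared with units that have other stays or screening intervals. A difference in stay between bathing periods would also leak into the comparison.

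**Working it through.** **Inputs.** Swab interval 14 days (5.7). About 800 patients (synopsis). 37,096 patient days required and an annual census of 45,000 patient days (5.9). No MDRO rate and no mean stay are given, so true rates of 2, 5 and 10 per 1000 days are assumed below.

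**The plan's own figure.** The 37,096 days come from the bloodstream-infection sample size. Two proportions of 2.5 and 1.25 per 1000, two-sided 0.05, 80% power, give 18,801 per group against the stated 18,548 (+1.4%), so that figure reproduces. It says nothing about MDRO and serves here only to bracket the stay:
- 37,096 / 800 = 46.4 days per patient
- 2 × 45,000 / 800 = 112.5 days per patient. The census covers the whole unit, including infants who are not eligible, so this is a generous figure.
- 20 days is a pure assumption, added to show a short stay.

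**Share of time that is seen.** Take exponential stay with mean m and swab rounds every 14 days at random phase. At any moment the remaining stay is again exponential, and the next round is uniform on 0 to 14 days. The chance that a swab follows before discharge is

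S = (m/14) × (1 − exp(−14/m)).

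Under this model S is also the share of infants swabbed at least once.

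| Mean stay m | S | Unseen, 1 − S = shortfall in B |
|---|---|---|
| 20 days | 0.719 | 28% |
| 46.4 days | 0.863 | 14% |
| 112.5 days | 0.940 | 6% |

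Simulation agrees: B is 13.5% to 13.8% low at 46.4 days and about 6% low at 112.5 days, for all three true rates. With fixed or gamma stays the shortfall in B is 12% to 15% at 46.4 days, so it does not hinge on the exponential form.

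**Outcome C.** Two errors act together. Unseen time lowers the rate. Removing all days of identified infants, including those before colonisation, shrinks the denominator and raises it. With exponential stay and 14-day swabs:

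| Mean stay | True rate per 1000 | C as written | Error |
|---|---|---|---|
| 46.4 | 2 | – | −7% |
| 46.4 | 5 | 5.1 | +3% |
| 46.4 | 10 | 11.8 | +18% |
| 20 | 10 | 8.1 | −19% |
| 112.5 | 10 | 18.5 | +85% |

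If only the days after identification were removed, C would be low throughout: −15%, −16% and −19% at 46.4 days for true rates of 2, 5 and 10.

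**Comparison between periods.** With equal stay, S is the same in both kinds of period and cancels. For means of 46 and 40 days (assumed), S is 0.863 and 0.844, and 0.844 / 0.863 = 0.978, a distortion of about 2%. For a true ratio of 5 to 10 per 1000 at 46.4 days, removing only days after identification gives (5 × 0.836) / (10 × 0.813) = 0.51 instead of 0.50. C as written gives 5.13 / 11.82 = 0.43. That larger shift comes from removing pre-colonisation days, not from the unseen tail.

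**Checking the remedy.** At a true rate of 10 per 1000, ending time at risk at the first positive or last negative swab gives 9.4 at every stay tested. Dating acquisition at the midpoint between the last negative and first positive swab gives 10.0. Either removes the dependence on length of stay; the midpoint also removes the remaining 6%.

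**If twice-weekly screening applied.** With a 3.5-day interval, B is only 1% to 7% low for mean stays of 25 to 112.5 days.

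**The case against.** The strongest reply is that the trial compares bathing periods, the swab schedule is the same in both, and these are secondary outcomes. That stands: it limits the point to absolute rates and event counts, with about 2% on the ratio in the example above.

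Three stronger readings are tempting and not supported.

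- A reader might infer that all the MDRO rates are 14% to 28% too low. The upper figure needs a 20-day stay. The preliminary phase's 200 patient days for up to 20 infants per group (10 days each if 20 enrol) is a planning minimum, not a measured stay. The protocol's totals also allow 6%. C as written can be too high.
- A reader might take the 79 against 60 days in section 4 as evidence that chlorhexidine periods will have shorter stays, and so an artefactual reduction. That figure compares infants with and without sepsis in a cited US population. It says nothing about stay by bathing period.
- A reader might infer that D follows infants as negative to discharge. The text states no censoring date, and such a rule may sit in an analysis plan that is not shown.

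It is also fair to say that two-weekly swabs may not be the only route. Section 4 describes more frequent screening and section 5.7 a daily culture review. But section 5.7 is the text that governs the study period, and the culture review is stated for infections. What remains is a conflict to resolve, not a rebuttal.

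Nor can the denominators be left to an analysis plan: section 5.6 writes them out.

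**Conclusion.** The point holds in limited form. The written denominators of B and C include infants and days with no ascertainment. B is low by about 6% to 14% at the mean stays that the protocol's totals imply, and by up to 28% if the mean stay were 20 days. This assumes exponential stay, two-weekly rounds at random phase, perfectly sensitive swabs and no detection by other cultures. The net direction for C is not fixed: at 46 days and true rates of 5 to 10 per 1000, it runs from nearly unbiased to +18%. Two opposing errors of unknown size do not make C a valid rate. The unseen tail barely affects the intervention-control comparison unless stays differ materially. For D the matter is one of clarification. Overall this is a minor-to-moderate error in secondary outcomes.

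**What to change.** In section 5.6:

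1. Define time at risk for C as days up to the first positive swab, or to the midpoint between the last negative and first positive swab, for colonised infants, and up to the last negative swab for all others. This also replaces the subtraction of all days of identified infants. The midpoint performed better in the check above.
2. State that D is censored at the last negative swab.
3. Give B among infants with at least one study swab, and report the number never swabbed by bathing period. Describe B as detected colonisation. Restricting it to swabbed infants does not recover acquisitions after the last swab: with a fixed 50-day stay nobody goes unswabbed, yet at 10 per 1000 B is still about 11% low.
4. Reconcile the two-weekly schedule in section 5.7 with the twice-a-week screening in section 4, and say which swabs feed the outcomes.

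The cost is wording plus the date of each swab, including negative ones. The hospital laboratory that processes the swabs should hold these dates, but they should be named as a data item. No extra swabs are needed. Roughly 6% to 28% of patient days, which carry no colonisation information, leave the denominator, and infants with short stays leave B.

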**5.7 Data collection**

Each patient admitted to the NICU during the study periods and meeting the inclusion criteria, will be recorded and assigned a specific study number. The dates of admission and dates of discharge will be recorded and used to calculate length of stay and to determine the

incidence of nosocomial infections based on microbiological data. Clinical and laboratory data, including the use of invasive device (intravascular devices, mechanical ventilation, feeding tubes) will be collected on standardized forms. The data will be coded under a password protected database and linked only to study patient identifier.

Infections and MDRO acquisitions will be monitored during the study period. Events occurring within 2 days after the transition will be assigned to the previous bathing period.

For infection surveillance, daily review of cultures and new orders for antibiotic therapy will be performed for all study participants. Infectious events will be evaluated by an independent investigator blinded to the intervention period.

Active surveillance testing for MDRO will be performed once every two weeks during the study period. Swabs from the nasopharynx (for MRSA)] and from the rectal area (for ESBL producing organisms, VRE and CRAB) will be obtained by unit staff and processed in the microbiology laboratory of Shaare-Zedek Medical Center.

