The emergence of multidrug- resistant organisms (MDRO) in acute-care settings, including the neonatal intensive care unit (NICU) , complicates the antimicrobial therapy and highlights the urgent need to limit the spread of such organisms and reduce the rate of NIs. Resistant organisms such as methicillin-resistant *Staphylococcus aureus* (MRSA), extended-spectrum beta-lactamase producing enterobacteriacae (ESBL) and carbapenem resistant *Acinetobacter baumanii* (CRAB) have caused outbreaks with associated morbidity and mortality in NICUs around the world ^[[7]](#endnote-7)^’^[[8]](#endnote-8)^’^[[9]](#endnote-9)^ . A stay in the NICU for > 1 week is a prominent predictor of colonization with resistant organisms^[[10]](#endnote-10)^. Strategies that have been utilized to limit the spread of MDRO within ICU’s have included stricter attention to barrier precautions following identification of patients colonized with these organisms, as well as improved handwashing. One prominent strategy that has emerged as recommended by recent SHEA guidelines ^[[11]](#endnote-11)^suggests that hospitals should adopt more aggressive active surveillance culturing to identify patients colonized with MDRO at the time of admission and periodically during their hospital stay. It is advocated, that under this “search and isolate” strategy, once reservoirs of resistant organisms within the hospital are identified, nosocomial transmission can be effectively eliminated through the use of strict barrier precautions and hand hygiene for these previously unidentified patients. However, this “search and isolate” strategy has multiple flaws. First, it is costly and requires high level of compliance with contact precautions and hand hygiene among healthcare personnel. Second, this strategy does little to eradicate colonization.

*As long as patients remain colonized, the opportunity for transmission exists. Therefore, a strategy that may address skin carriage of pathogens has the potential to reduce horizontal transfer to other patients as well as reduce the colonized patient’s risk to develop infection.*

The guidelines for preventing intravascular catheter-related infections published by the Centers for Disease Control and Prevention (CDC) recommend daily skin cleansing of ICU patients with 2% chlorhexidine to reduce catheter-related bloodstream infections (BSI)^[[12]](#endnote-12)^, but could not recommend its use in infants < 2 months of age due to lack of safety and efficacy data.

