**5.2 Design**

This is a prospective, controlled; crossover study of daily bathing with no-rinse, 2% CHG impregnated washcloths versus bathing with water/soap or water according to gestational age and weight (e.g. standard bathing).

The primary study outcome is CLABSI/ BSI and clinical (culture-negative) sepsis.

Secondary study outcomes are rate and time to colonization with pathogenic bacteria.

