**5.5 Intervention**

All infants in the NICU eligible for the study will be assigned for bathing three times a week with washcloths impregnated with 2% chlorhexidine gluconate (Clinell ® Chlorhexidine wash cloths, GAMA healthcare) during the initial 6-months study period (intervention), followed by standard bathing during the second 6-months period, then again intervention period for 6 months and standard bathing for 6-months. Total study period- 2 years.

**Inclusion criteria**: infants weighing ≥1500 grams and ≥10 days of age; parents’ informed consent

**Exclusion criteria:** infants weighing <1500 grams or <10 days of age**;** parents’ refusal to sign informed consent.

For standard bathing procedure see appendix 1.

Before the study initiation, as well as at the beginning of each study period, nurses will be instructed on the proper technique for bathing patients. Bathing will be performed according to product brochure, three times a week.

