Appendix 1.

Standard Bathing procedures

| **Gestational week** | **Age at Onset of Bathing** | **Frequency** | **Product** |
| --- | --- | --- | --- |
| <26 | 3 weeks | Once a week | Water |
| 27-30 | 2 weeks | Once a week | Water |
| 31-32 | 1 week | Three times a week | Water |
| >=33 | 1 week | Three times a week | Water+mild soap |
| Term | Day 2 | Three times a week | Water+mild soap |

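### The 2-day switch rule is applied to MDRO acquisitions that are swabbed for only every two weeks, so acquisitions under the old bath can be counted for the new one; for bloodstream infection and sepsis the missing washout is a smaller matter

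*Protocol*

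**What the plan says.** The unit alternates between chlorhexidine and standard bathing in four six-month periods, chlorhexidine first: "followed by standard bathing during the second 6-months period, then again intervention period for 6 months and standard bathing for 6-months" (Protocol 5.5), "Total study period- 2 years". There are three switches: two from chlorhexidine to standard bathing and one the other way.

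Protocol 5.7 introduces the monitoring of infections and MDRO acquisitions together and then gives one attribution rule for both: "Events occurring within 2 days after the transition will be assigned to the previous bathing period". It states no washout and does not say whether patient-days move with the reassigned events. It then sets MDRO surveillance swabs at one every two weeks.

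Outcomes B, C and D in 5.6 are all MDRO colonisation outcomes (per patient, per eligible patient-days, and time to colonisation). Section 5.9 adds a Cox model for MDRO acquisition by period.

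The bath frequency is described in more than one way. Section 5.5 says "Bathing will be performed according to product brochure, three times a week"; 5.2 calls the trial a "crossover study of daily bathing with no-rinse, 2% CHG impregnated washcloths". The Synopsis uses both descriptions, and its treatment row gives three baths a week for both arms. Appendix 1 has standard-bathing rows such as ">=33 | 1 week | Three times a week | Water+mild soap" and "27-30 | 2 weeks | Once a week | Water".

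**The concern.** A rule that assigns events to periods should be at least as long as the delay between the event and its detection. For bloodstream infection that delay is short and two days is a recognisable choice. For MDRO acquisition the delay is set by the swab schedule and can reach 14 days. A first positive swab on day 10 of a new period, after a negative swab four days before the switch, says nothing about which bath the infant was receiving when colonised. The rule counts it for the new bath.

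The protocol's own mechanism makes a second question reasonable for the primary outcome. The hypothesis in 5.1 runs through skin colonisation and spread in the ward, and the Background says "As long as patients remain colonized, the opportunity for transmission exists" and describes residual activity of chlorhexidine on the skin. Infants colonised or protected under the old bath remain in the unit after a switch, and a 2-day rule does not deal with them. Events still driven by the old bath would then dilute the comparison of bloodstream infection and sepsis rates.

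**Working it through.** **MDRO outcomes.** Inputs from 5.7: a rule of 2 days and a swab interval of 14 days. Assumption: swab days are spread evenly relative to the switch.

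- Share of first post-switch swabs after day 2: (14 − 2)/14 = 12/14 = 86%.
- A swab on day *d* after the switch covers 14 − *d* days under the old bath. Averaged over swabs after day 2, the old-bath time credited to the new period is (12²/2)/14 = 5.14 days per infant present. The reverse error, from swabs within 2 days, is (2²/2)/14 = 0.14 day.
- Together that is 5.29 days per switch, or 5.29/182.6 = 2.9% of a six-month period.

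The protocol gives no MDRO acquisition rate or expected effect. For illustration only, suppose chlorhexidine halves acquisition and take the two middle periods, which have a switch at each end. Each is shifted by 5.29 × 0.5 = 2.64 day-equivalents toward the other bath. The standard rate becomes 1 − 2.64/182.6 = 0.986 and the chlorhexidine rate 0.50 + 2.64/182.6 = 0.514, a ratio of 0.522. For the first and last periods the net shift also depends on how the first swab of the study and acquisitions after the last swab are handled, so I give no overall figure.

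**The plan's sample size.** Section 5.9 gives 18,548 patient-days per group for a 50% reduction from 2–3 bloodstream infections per 1000 patient-days, with 80% power and a 0.05 level. The pooled two-proportion formula is

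n = [z(α)·√(2p̄(1−p̄)) + z(β)·√(p₁(1−p₁) + p₂(1−p₂))]² / (p₁−p₂)².

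At 2.5 vs 1.25 per 1000, two-sided, it gives 18,801 (+1.4%). At 2.0 vs 1.0, one-sided, it gives 18,519 (−0.2%). The figure is reproduced, though sidedness is not settled. I use 2.5 vs 1.25, two-sided, where 18,548 per group gives 79.5% power.

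**Bath intervals against the 2-day rule.** Three baths a week, evenly spread, give gaps of 2, 2 and 3 days (mean 7/3 = 2.33). A switch at a random time leaves more than 2 days to the first new bath with probability 1/7. On a weekly schedule the probability is 5/7, and this can arise only at the two switches into standard bathing.

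**Carry-over in the primary rate.** Let P = 182.6 days per period, let the true ratio be 0.50, and let the old bath's rate persist for *k* days after each switch. Move the first 2 days' events and patient-days to the old period. With the standard rate set to 1:

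- chlorhexidine rate = [0.5(2P + 4 − k) + (k − 2)] / (2P + 2)
- standard rate = (2P − k) / (2P − 2)

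| *k* (days) | Chlorhexidine | Standard | Observed ratio | Power at 18,548 per group |
|---|---|---|---|---|
| 3 | 0.501 | 0.997 | 0.503 | 78.8% |
| 7 | 0.507 | 0.986 | 0.514 | 76.3% |
| 14 | 0.516 | 0.967 | 0.534 | 71.3% |
| 28 | 0.535 | 0.928 | 0.577 | 60.0% |

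The rows for 3 and 7 days match the longest bath gaps. Those for 14 and 28 days are assumptions.

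**Cost of a 14-day exclusion.** It removes 3 × 14 = 42 of 730 days (5.8%): 14 days of chlorhexidine time and 28 of standard time. Applied to the primary rate with no carry-over, power falls from 79.5% to 77.2%.

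**The case against.** A reader might infer that the rule is shorter than the bath interval in both arms, so that events after each switch are generally credited to a bath the infant has not had. The documents do not support that. Two of the three evenly spread gaps equal 2 days, and under the daily wording the rule is longer than the gap. Events of the first 2 days go to the old period in any case. The once-a-week rows conflict with the Synopsis treatment row, and the protocol does not show how many eligible infants would fall in them.

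A reader might also infer that a null primary result could not be told apart from carry-over. The figures do not bear this out: even a 28-day carry-over would show a halved rate as 0.577. The protocol gives no duration for residual activity, so the longer scenarios are unsupported. Nor does a 14-day washout of the primary comparison clearly pay for itself: the power it leaves (77.2%) is close to what a 7-day carry-over leaves (76.3%).

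These objections stand, and they reduce the infection part to a sensitivity question. They do not touch the MDRO part, which depends on the swab interval and not on the bath schedule. The twice-weekly screening that section 4 describes as existing unit policy would not rescue the rule either, since its gaps of 3 to 4 days also exceed 2 days.

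**Conclusion.** The point holds for the MDRO outcomes. A 2-day rule cannot assign to a period an event seen only every 14 days. About 12 of 14 first post-switch swabs escape it, given evenly spread swab days. Acquisitions from the old bath enter the new period's count at all three switches, which tends to pull outcomes B, C and D and the MDRO Cox analysis toward no difference. About 5 days of exposure per infant present are misplaced at each switch. The effect is modest, but it follows from a stated rule and is avoidable.

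For bloodstream infection and sepsis the absence of a washout is real but minor on what the protocol documents: 0.503 to 0.514 for a true 0.50. The larger values, 0.534 and 0.577, rest on an assumed carry-over of 14 or 28 days. Dilution of this kind works against finding a benefit and does not create one.

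Two further defects belong to the same text. The rule moves events but is silent on the matching patient-days (2 × 3 = 6 of 730 days, 0.8%), and the bath frequency is stated inconsistently.

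**What to change.** In Protocol 5.7:

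1. Limit the 2-day reassignment to infections, and state that the matching patient-days move with the events.
2. For MDRO outcomes, leave out the first 14 days after each switch (one surveillance cycle), both acquisitions and patient-days. Alternatively, count an acquisition for the new period only if the infant had a negative swab after the switch, with time at risk starting at that swab.
3. Keep the primary rate as planned and add two sensitivity analyses: one leaving out the first 14 days after each of the three switches, and one limited to infants whose participation began in the current period.

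The statements of daily, three-times-a-week and once-a-week bathing in the Synopsis, 5.2, 5.5 and Appendix 1 must be reconciled.

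The cost is about 42 of 730 days (6%) of MDRO follow-up under the exclusion option, and a little more analysis. Bathing, swabbing and data collection do not change, and no more infants are needed.
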